# Radiation therapy alone versus radiation therapy plus radiofrequency ablation/vertebral augmentation for spine metastasis: study protocol for a randomized controlled trial

**DOI:** 10.1186/s13063-020-04895-x

**Published:** 2020-11-23

**Keywords:** Radiation therapy, Radiofrequency ablation, Vertebral augmentation, Spine, Vertebrae, Bone metastasis, Randomized controlled trial

## Abstract

**Background:**

Spine metastasis is a common occurrence in cancer patients and results in pain, neurologic deficits, decline in performance status, disability, inferior quality of life (QOL), and reduction in ability to receive cancer-directed therapies. Conventional external beam radiation therapy (EBRT) is associated with modest rates of pain relief, high rates of disease recurrence, low response rates for those with radioresistant histologies, and limited improvement in neurologic deficits. The addition of radiofrequency ablation/percutaneous vertebral augmentation (RFA/PVA) to index sites together with EBRT may improve pain response rates and corresponding quality of life.

**Methods/design:**

This is a single-center, prospective, randomized, controlled trial in patients with spine metastasis from T5-L5, stratified according to tumor type (radioresistant vs. radiosensitive) in which patients in each stratum will be randomized in a 2:1 ratio to either RFA/PVA and EBRT or EBRT alone. All patients will be treated with EBRT to a dose of 20–30 Gy in 5–10 fractions. The target parameters will be measured and recorded at the baseline clinic visit, and daily at home with collection of weekly measurements at 1, 2, and 3 weeks after treatment, and at 3, 6, 12, and 24 months following treatment with imaging and QOL assessments.

**Discussion:**

The primary objective of this randomized trial is to determine whether RFA/PVA in addition to EBRT improves pain control compared to palliative EBRT alone for patients with spine metastasis, defined as complete or partial pain relief (measured using the Numerical Rating Pain Scale [NRPS]) at 3 months. Secondary objectives include determining whether combined modality treatment improves the rapidity of pain response, duration of pain response, patient reported pain impact, health utility, and overall QOL.

**Trial registration:**

ClinicalTrials.gov NCT04375891. Registered on 5 May 2020.

## Background

Metastasis to the spine is a common complication of cancer, with approximately 40% of patients developing clinically significant disease. In autopsy series, up to 90% of patients with metastatic cancer have been identified as having micrometastatic spine disease [1]. Bone pain from spine metastasis is associated with increasing disability rates in these patients [2]. Furthermore, unlike other bone metastasis, spine metastasis results in vertebral body instability, sensory and motor neurologic deficits, and spinal cord or cauda equina compression, which can compromise a patient’s functional status and ability to receive other cancer-directed therapies. The standard treatment for patients with spine metastasis is fractionated external beam radiotherapy (EBRT), typically delivered in 1–10 fractions. The Radiation Therapy Oncology Group (RTOG) 97-14 trial randomized patients with bone metastasis (including spine disease) to 8 Gy in 1 fraction or 30 Gy in 10 fractions and demonstrated comparable outcomes between both arms, leading to the utilization of both schedules in clinical practice [3]. However, the duration and rate of pain control for the subset of patients with spine metastasis in both arms was quite modest, with only 61% of patients reporting complete or partial pain relief 1 month post-treatment. An alternative approach for patients with localized spine metastasis is spine stereotactic radiosurgery (SRS). Although retrospective series with this technique are promising, they remain unvalidated in the absence of prospective randomized data [4]. In addition, it is unclear how many patients are eligible for this highly precise treatment given that more than 50% of patients with spine metastasis have involvement across multiple levels and up to 38% have involvement of multiple, non-contiguous segments [5]. Further, there is a defined rate of late vertebral collapse consequential to SRS, which can worsen clinical symptoms.

Radiofrequency ablation, with or without percutaneous vertebral augmentation (RFA/PVA), has been used to treat pathologic fractures associated with spine metastasis with high rates of initial pain response [6]. Using this technique, disease in the central portion of the vertebral body, or that approaching the posterior elements, is first treated with lethal thermal radiofrequency (RF) energy, and the remaining bone is reinforced with cement to provide stability. Retrospective series have demonstrated significant early pain response and reduction in narcotic use as early as 1 week post-treatment [7]. Investigation into the benefits of a multi-modality approach is warranted, as RFA offers rapid pain relief but has limited oncologic effect by not addressing the entirety of the vertebral metastatic disease, especially in lesions in paraspinal locations and with disease in posterior elements. A small, non-randomized feasibility study of RFA and EBRT forms the basis of the combined modality approach investigated in this trial. In this study of 15 patients with bone metastasis and a pre-treatment pain score of at least 5 treated with RFA and EBRT (20 Gy in 5 fractions) matched to patients treated with EBRT alone, higher rates of complete pain response (53.3 vs. 16.6%, *p* = 0.027) and overall pain response (93.3 vs. 59.9%, *p* = 0.048) were observed [8]. This study was limited by the RF technology available at the time, lack of PVA in at-risk patients, as well as small sample size; therefore, further randomized prospective evidence is needed to characterize the benefits of modern combined modality techniques.

The primary objective of this randomized, controlled trial is to determine whether RFA/PVA in addition to EBRT improves pain control compared to EBRT alone for patients with spine metastasis. Secondary objectives include determining whether combined modality treatment improves the rapidity of pain response, duration of pain response, patient reported pain impact, health utility, and overall quality of life (QOL).

## Methods/design/interventions

This study is a single-center, prospective, randomized, controlled trial of patients with spine metastasis with two arms. The study protocol has been reported in accordance with the Standard Protocol Items: Recommendations for Clinical Interventional Trials (SPIRIT) guidelines (see Additional file 1). Eligible patients will have spine metastasis from T5 to L5 (within the treatment limits of RFA/PVA). There is no limit to the maximal involvement of contiguous vertebral bodies with metastatic disease, as long as an index lesion of pain can be determined and fewer than two sites would undergo RFA/PVA in total. All patients will undergo an MRI of the involved spine within 6 weeks prior to registration to determine the extent of spine involvement and must score their index lesion-associated pain as at least 5 using the Numerical Rating Pain Scale (NRPS). In the control arm, patients will receive conventional palliative EBRT to any of the following dose and fractionation schedules per the discretion of the treating physician: 20 Gy in 5 fractions, 24 Gy in 6 fractions, and 30 Gy in 10 fractions. Single fraction radiotherapy is not allowed in this study since this has been associated with higher incidence of re-treatment [9] and that fractionated regimens are more traditionally used in patients who have undergone percutaneous or surgical interventions. Patients randomized to the experimental arm will undergo RFA/PVA followed by EBRT using the same dose/fractionation schedules. All supportive therapy for optimal medical care will be given during the study period at the discretion of the attending physician(s) within the parameters of the protocol and documented as concomitant medications. Chemotherapy is not permitted within 24 h prior to or concurrently with EBRT. In addition, the patient can receive chemotherapy no earlier than 24 h after EBRT. If a deviation from the protocol occurs, the PI will complete and electronically submit the “Protocol Deviation Form.”

The target parameters will be measured and recorded at the baseline clinic visit (on the day of treatment) and daily at home with collection of weekly measurements at 1, 2, and 3 weeks after treatment, and at 3, 6, 12, and 24 months following treatment with imaging and QOL assessments (see Table 1). There will be no special criteria for discontinuing or modifying allocated interventions given that both are standard of care interventions (Fig. 1).

**Table 1 Tab1:** Study parameter table

Assessments	Pre-treatment	1 month from randomization	Follow-up: At 3, 6, 12, 24 months from randomization
History/physical	Within 2 weeks prior to registration		X
Performance status	Baseline		X
Neurological exam	Within 1 week prior to registration		X
Imaging of the spine (CT scan/bone scan is allowed, MRI preferred)	Within 6 weeks prior to registration		X
Numerical rating pain scale and documentation of patient’s pain medication^a^	Within 1 week prior to registration	(On the day of treatment) (At home: Daily with cumulative weekly measurements at 1, 2, and 3 weeks; bring to clinic at 1 month) In clinic at 1 month	X
FACT-G (FA), BPI (QL), EQ-5D (HP)	Baseline		At 3, 6, 12, and 24 months from randomization
Adverse event evaluation		X	X

^a^NRPS at 3 months is required for analysis of the primary endpoint

**Fig. 1 Fig1:**
[figure not shown]
Flowchart of the clinical trial

### Recruitment and randomization

All patients will be enrolled in this trial at the treating institution, Baptist Health South Florida, Inc. Patients will be provided with information about this study by the medical personnel and research staff in the radiation oncology department when evaluated in consultation for palliative EBRT to spine metastasis. The medical charts of interested patients will be reviewed by the research staff to ensure each patient meets eligibility criteria. Radiation oncologists will discuss patient eligibility for the trial with the interventional radiology and neurosurgical teams and review relevant imaging to determine the sites for RFA/PVA. Patients will also meet with the procedural team, either neurosurgery or interventional radiology, to discuss the logistics, risks, and benefits of the procedure. Given this patient population with metastatic disease and the follow-up intervals occurring at routine time points and coordinated with imaging studies, it is expected that the combination of these will help boost participant retention and completion of follow-up events. All patients who enroll onto this clinical trial will sign an informed consent document which outlines the research study in detail. The principal investigator or sub-investigators will describe the study to the patient and obtain written informed consent.

Patients enrolled onto this trial will be stratified according to the tumor type (radioresistant [soft tissue sarcoma, melanoma, and renal cell carcinoma] versus other non-hematologic tumor histologies). The treatment allocation scheme will be used for randomization to balances these patient factors [10]. Within each stratum, patients will be randomized in a 2:1 ratio to either RFA/PVA and EBRT or EBRT alone. This unequal randomization was chosen given the well-known and documented pain response rates to EBRT, accommodates increased demand for combined modality treatment, allows for a larger sample in the combined modality group to evaluate for potential adverse events, and follows the paradigm established by RTOG 0631. The randomization will be performed by a statistician using stratified permuted block randomization. Allocation concealment technique will be used to prevent selection bias and will be performed on an offsite computer. The recruitment phase will conclude when 52 patients have enrolled in the trial (35 in the RFA/PVA and EBRT arm and 17 in the EBRT alone arm), and it is expected that accrual should be completed over a course of 18 months.

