### Statistical analysis

Based on the reported incidence of complete or partial pain response from the results of the feasibility matched cohort study of RFA/PVA and EBRT [8], with a two-sided *α* = 0.05 and *β* = 0.20 and a study design of 2:1 randomization scheme (RT plus PVA/RFA:RT), the study will be adequately powered with 52 patients (35 in the RT plus PVA/RFA arm and 17 in the RT arm). Assuming a 5% ineligibility rate, a death rate of 15%, and a patient non-compliance rate of 15%, the total sample size required would be 80 patients. No interim analyses with treatment efficacy results are planned. The primary endpoint is complete or partial pain response at 3 months after randomization, and all eligible, randomized patients will be included in the analysis regardless of treatment compliance (intent-to-treat analysis). Descriptive statistics of the actual change scores, mean change scores, and standard deviations will also be reported. For analysis of the secondary pain response endpoints (rapidity of pain response and duration of pain response), the median time to each outcome variable will be estimated using the Kaplan-Meier approach, the stratified log-rank test will be used to test for statistically significant differences with an α = 0.025, and the Cox proportional hazards regression model will be used to determine hazard ratios and 95% confidence intervals for the treatment differences. Moreover, unadjusted ratios and adjusted ratios for radiosensitive vs. radioresistant histology will be computed. The incidence of adverse events will be reported according to CTCAE v5.0, and differences in the rates at 3 months between the two treatment arms will be tested using the two-sided chi-square test at the 0.05 significance level. To analyze differences in QOL, global pain, and health utility, changes in FACT-G, BPI, and EQ-5D will be described with longitudinal data analysis. The mean differences will be compared across the treatment arms using the two sample *t* test at the 0.025 significance level. The relationship between treatment response and QOL will also be analyzed using the two sample *t* test at the 0.025 significance level.

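### Recruitment is set to end at 52 enrolled patients, but the sample-size paragraph treats 52 as the number needed before losses and requires 80 in total; the two must be reconciled.

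*Protocol article*

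**What the plan says.** Under Statistical analysis, the calculation is made "with a two-sided *α* = 0.05 and *β* = 0.20", with 2:1 allocation, and takes its response rates from the earlier feasibility study: "Based on the reported incidence of complete or partial pain response from the results of the feasibility matched cohort study". The Background reports those rates as "overall pain response (93.3 vs. 59.9" percent. On that basis "the study will be adequately powered with 52 patients (35 in the RT plus PVA/RFA arm and 17 in the RT arm"). The next sentence adds an allowance for losses: "Assuming a 5% ineligibility rate, a death rate of 15%, and a patient non-compliance rate of 15" percent, and concludes that "the total sample size required would be 80 patients".

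Under Recruitment and randomization, the stopping point for accrual is different: "The recruitment phase will conclude when 52 patients have enrolled in the trial", with the same 35 and 17 per arm. That sentence also expects accrual to take 18 months. The figure of 80 appears only under Statistical analysis. Trial status repeats the 18 months without a patient number.

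On who is analysed, Statistical analysis says that every eligible randomized patient enters the primary analysis, whether or not the patient complied with treatment.

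**The concern.** The number at which a single centre closes accrual determines the power of the trial. The article uses one figure, 52 split 35:17, in two roles: as the analysable number that delivers 80% power, and as the enrolment number at which recruitment ends. These coincide only if nobody is lost, and the article itself expects losses adding up to 35%. If the recruitment sentence is followed, the trial cannot be expected to deliver its stated beta of 0.20, and a non-significant primary result would be hard to interpret. The article reports that accrual is already open, so the point has practical urgency.

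**Working it through.** **Inputs.** Response 0.933 (combined) and 0.599 (EBRT alone), from the Background. Two-sided alpha 0.05, power 80%, allocation 2:1 and losses of 5%, 15% and 15%, from Statistical analysis.

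**Step 1: reproduce the 52.** The pooled-variance two-proportion formula without continuity correction gives 17 + 34 = 51, against the stated 52. For power at given arm sizes n1 (EBRT) and n2 (combined):

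power = Φ{ [d − 1.96·√(p̄(1−p̄)(1/n1+1/n2))] / √(p1(1−p1)/n1 + p2(1−p2)/n2) }, where d = 0.933 − 0.599 = 0.334 and p̄ is the weighted mean response.

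At 17 and 35: p̄ = (17×0.599 + 35×0.933)/52 = 0.824. The pooled standard error is 0.1126 and the unpooled one 0.1262. So power = Φ[(0.334 − 1.96×0.1126)/0.1262] = Φ(0.90) = 81.5%. Exact power with Fisher's test is 80.1%. So 52 is the size for 80% power with no losses.

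**Step 2: reproduce the 80.** 5% + 15% + 15% = 35%, and 52/(1 − 0.35) = 80.0. So 80 is 52 inflated by treating all three categories as lost to analysis. (Compounding them would give 52/(0.95×0.85×0.85) = 75.8, or 76.)

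**Step 3: apply the same losses to 52 enrolled.**

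- All three lost, additive: 52×0.65 = 33.8, about 34 (23:11).
- All three lost, compounded: 52×0.95×0.85×0.85 = 35.7, about 36 (24:12).
- Only ineligible patients and deaths lost: 52×0.95×0.85 = 42.0 (28:14).
- Only ineligible patients lost: 52×0.95 = 49.4, about 49 (33:16).

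| Analysed (combined:EBRT) | Normal approximation | Fisher exact |
|---|---|---|
| 35:17 (no losses) | 81.5% | 80.1% |
| 33:16 | 79.4% | 77.3% |
| 28:14 | 73.7% | 71.3% |
| 24:12 | 67.6% | 63.7% |
| 23:11 | 65.1% | 58.6% |

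For example, at 23:11 the formula gives Φ[(0.334 − 1.96×0.1393)/0.1567] = Φ(0.39) = 65.1%. The exact power of the uncorrected chi-square test is 69.6% at 23:11, 69.2% at 24:12 and 73.8% at 28:14, so a choice among these tests does not close the gap.

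**Step 4: accrual.** 52/18 = 2.9 patients per month; 80/18 = 4.4 per month. At 2.9 per month, 80 patients would take about 28 months.

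**The case against.** Four points can fairly be made on the other side.

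First, a reader might infer that stopping at 52 simply means 59-65% power (23:11 in the table). The documents do not support so flat a statement. It requires all three kinds of loss to leave the analysis. The inflation to 80 assumes that, but the intent-to-treat sentence keeps eligible patients in regardless of compliance. If non-compliant patients supply a 3-month pain score, only ineligibility and death remove patients, and power is about 71-74%. That figure in turn assumes that non-compliance does not dilute the effect. This objection stands on the size of the shortfall but not on its existence.

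Second, a reader might go further and count deaths and non-compliers as non-responders. Scaling both rates by 0.70 (0.653 against 0.419) gives 35.8% (Fisher 28.8%) at 35:17. This should not be attributed to the 52/80 conflict. The article states no such imputation, and the same assumption gives only 51.6% (Fisher 46.4%) with 80 enrolled at 53:27. Most of the fall from 80% therefore comes from the imputation and not from stopping at 52.

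Third, the article condenses a full protocol that is not shown, and the recruitment sentence may be a drafting slip while the trial works to 80. That is possible, so nothing here shows that the trial will in fact stop at 52. But both figures stand in current running text, and no separate document can make both sentences true.

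Fourth, the recruitment sentence might be read as meaning 52 evaluable patients. It says enrolled, and nothing in it provides for replacing patients who are lost.

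**Conclusion.** The contradiction is explicit, and nothing in the article resolves it. Its own arithmetic shows that 52 is the pre-loss size and 80 the total required. If recruitment ends at 52, power under the article's response rates is about 59-68% when all three losses leave the analysis (Fisher to normal approximation, additive or compounded losses). It is about 71-74% when non-compliant patients are analysed without dilution. Even if ineligible patients are the only loss, it is 77-79% on the same two methods, but that ignores two of the three losses the article counts. The direction is therefore secure. The size depends on a question the article leaves open, namely which losses leave the analysis. The documents do not establish which of the two targets governs in practice.

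**What to change.** Make the two sections agree, in one of two ways:

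- Change the recruitment sentence so that accrual ends at 80 randomized patients (2:1, about 53:27), to leave about 52 for analysis (80×0.65 = 52). This asks for no more patients than Statistical analysis already requires.
- If 52 is the real cap, delete the 80 and restate power as about 59-74%, saying which of the three losses leave the analysis. The cost is a less favourable stated power.

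In either case, state whether the 18-month forecast refers to 52 patients (2.9 per month) or 80 (4.4 per month), and revise it if the rate is not realistic for the number kept. The first option is a wording correction, plus a longer accrual period if the forecast was built on 52. Because accrual is open, the correction should be made before enrolment reaches 52.

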### Inclusion criteria

The target population for this trial includes patients with metastatic disease to the spine, between T5 and L5, as detected by any imaging study. There is no limit on the maximal involvement of contiguous vertebral bodies of disease as long as the index lesion(s) can be treated with RFA/PVA and fewer than 2 sites need to undergo treatment in total. Patients must have a Zubrod performance status of 0–3 and can have other sites of visceral or osseous metastatic disease. Patients with epidural extension of disease are eligible for this study provided that there is ≥ 3-mm distance between the spinal cord and the edge of the metastasis. Key ineligibility criteria include metastatic disease from radiosensitive histologies (myeloma, lymphoma, small-cell lung cancer, or germ-cell tumors), those with frank spinal cord compression, or those with rapid neurologic decline or bony retropulsion necessitating urgent neurosurgical intervention.

### Assessment of the primary and secondary endpoints

The primary endpoint for this trial is pain response, defined as complete or partial pain relief, as measured using the NRPS at 3 months (post-treatment pain score of 0 or at least 3 NRPS points). The NRPS is a widely utilized assessment of pain intensity in oncologic clinics and has demonstrated reliability in studies of small sample sizes and in settings where repeated measurements are obtained to monitor changes in pain intensity over time [11]. Using this scale, complete pain relief is defined as a pain score of 0 with no increase in narcotic pain medication, and partial pain relief is defined as a reduction in numerical pain score of at least 2 points at the index site with no increase in pain medication.

Secondary pain response endpoints include the rapidity of pain response, as defined as the time from study entry to complete or partial pain relief, and duration of pain response, as defined as the time from complete or partial pain relief to pain worsening (≥ 3 NRPS points). To assess these outcomes, patients will complete the NRPS for each treatment site at the baseline clinic visit (on the day of treatment) and daily at home with weekly measurements at 1, 2, and 3 weeks after randomization in addition to a diary of their pain medication use and any side effects they experience related to the treatment. One month after treatment, patients will complete the NRPS, and at the clinic visit, the research team will consolidate the patients’ pain level scores, pain medications, and document adverse events. Imaging of the treated spine will be obtained at baseline and at 3, 6, 12, and 24 months after randomization to assess the response to treatment as well as subacute or long-term change of the vertebral bone.

The study hypothesis is that given the potential benefit of combined modality treatment in providing rapid and durable pain relief, QOL will improve after RFA/PVA and EBRT. Therefore, a number of QOL outcomes will also be prospectively collected in this study, including QOL, as measured by the Functional Assessment of Cancer Therapy (FACT-G) [12]; patient perception of pain, as measured by the Brief Pain Inventory (BPI) [13]; and health utilities, as measured by the EuroQol (EQ-5D) [14] at 3, 6, 12, and 24 months post-study randomization.

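### The primary endpoint is defined with two response thresholds (3 and 2 NRPS points), and its own sentence omits the medication conditions that the definitions after it impose

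*Protocol article*

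**What the plan says.** Three sentences in the protocol article, section Assessment of the primary and secondary endpoints, bear on the definition.

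- The primary-endpoint sentence names complete or partial relief and adds a gloss in parentheses: "as measured using the NRPS at 3 months (post-treatment pain score of 0 or at least 3 NRPS points". It gives no medication condition, and it does not say that the 3 points are a reduction.
- Complete response: "complete pain relief is defined as a pain score of 0 with no increase in narcotic pain medication".
- Partial response: "partial pain relief is defined as a reduction in numerical pain score of at least 2 points at the index site". The condition attached to it is that analgesic use has not gone up, and here it is not limited to narcotics.

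The endpoint is stated again in two places, neither with a threshold. Statistical analysis says "The primary endpoint is complete or partial pain response at 3 months after randomization". The Discussion part of the Abstract says "defined as complete or partial pain relief (measured using the Numerical Rating Pain Scale [NRPS]) at 3 months". A further figure of 3 points in the same assessment section defines pain worsening for the duration endpoint, which is a different quantity.

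Two other statements matter. For entry, patients "must score their index lesion-associated pain as at least 5 using the Numerical Rating Pain Scale (NRPS" (Methods/design/interventions). The planning rates come from the feasibility cohort in Background: "overall pain response (93.3 vs. 59.9%, *p* = 0.048) were observed".

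**The concern.** The first sentence says that the endpoint is complete or partial relief, so its parenthesis and the later definitions claim to describe the same quantity. They differ on the size of the reduction and on whether a rise in analgesics disqualifies a patient. Nobody can derive the primary variable from this text without choosing between them.

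The outcome is patient-reported and only one arm undergoes a procedure. If both definitions remain in force, the choice could be made after the data have been seen, and it would then be hard to defend. The choice also determines whether the planned response rates describe the endpoint that will be analysed.

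**Working it through.** **1. Do the sentences classify the same patient differently?** Baseline is at least 5, so a fall of exactly 2 leaves a score of at least 3 and can never be complete relief.

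| Patient at 3 months | Parenthesis (0, or 3 points) | Complete/partial definitions |
|---|---|---|
| Falls exactly 2, no medication increase | Non-responder | Responder (partial) |
| Falls 3 or more, score above 0, any pain medication increased | Responder | Non-responder |
| Score 0, narcotics increased | Responder | Non-responder |
| Score 0, only non-narcotic medication increased | Responder | Responder (complete) |

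The first three rows conflict; the fourth does not. The parenthesis is read here as a reduction of 3 points. Taken literally, a post-treatment score of at least 3 would not be a response at all.

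**2. Reproduce the planned sample size.** Inputs: 0.933 and 0.599 (Background); two-sided alpha 0.05, power 0.80, allocation 2:1 (Statistical analysis). Pooled formula without continuity correction, n in the control arm:

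n = [1.96·√(p̄(1−p̄)·1.5) + 0.8416·√(p₁(1−p₁) + p₂(1−p₂)/2)]² / (p₂−p₁)²

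With p̄ = (0.599 + 2×0.933)/3 = 0.8217, n = 16.5, so 17 + 34 = 51 against the stated 52. The inflation also reproduces: 52/(1 − 0.35) = 80. The sample-size arithmetic is not at fault.

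**3. Power with 35 and 17 patients.** Power = Φ[(|p₂−p₁| − 1.96·s₀)/s₁], where s₀ is the pooled and s₁ the unpooled standard error. At the planning rates s₀ = 0.1126 and s₁ = 0.1262, so power = Φ[(0.334 − 0.2208)/0.1262] = 0.815.

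**4. Illustration of the threshold's effect.** The article gives no distribution of change scores. Assume that they are normal, rounded to whole points, with a common SD of 1.5 to 3. A reduction of at least 2 then corresponds to a cut at 1.5, and at least 3 to a cut at 2.5. A rate p under one rule becomes Φ[z(p) − 1/SD] when moving from 2 to 3 points, and Φ[z(p) + 1/SD] when moving from 3 to 2. Here z(0.599) = 0.251 and z(0.933) = 1.499.

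| SD | Planning rates are 2-point, 3 applied: rates (combined vs EBRT) | Power | Planning rates are 3-point, 2 applied: rates (combined vs EBRT) | Power |
|---|---|---|---|---|
| 1.5 | 0.797 vs 0.339 | 0.913 | 0.985 vs 0.821 | 0.573 |
| 2.5 | 0.864 vs 0.441 | 0.891 | 0.971 vs 0.742 | 0.683 |
| 3 | 0.878 vs 0.467 | 0.882 | 0.967 vs 0.720 | 0.708 |

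**5. A check without the normal model.** Suppose instead that the stricter rule simply lowers the planning rates. A fall of 5 percentage points in both arms gives power 0.756, and 10 in both gives 0.708. A fall of 5 in the EBRT arm and 10 in the combined arm gives 0.587; the reverse gives 0.846. Again power can move either way.

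**The case against.** The parenthesis may be no more than shorthand for the full definitions that follow, with the medication conditions understood. That could explain the missing conditions. It cannot explain a different number of points: if one figure is a slip, the article does not show which. Nor is this a detail left to an analysis plan, because the two statements conflict in the text itself.

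Several stronger readings are tempting, and the document does not support them.

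- *The narcotic and general medication wordings contradict each other.* They belong to different components, and meeting either component is enough. A patient at 0 with only a non-narcotic increase is a responder on every reading. The same increase would disqualify a patient at score 1, which is uneven but not a contradiction.
- *The sample size is valid for only one threshold.* The planning rates can belong to at most one definition. But if they are 2-point rates, the model gives more power under the 3-point rule, so 52 evaluable patients would suffice under both.
- *The secondary endpoints are equally affected.* Rapidity and the start of duration use the terms complete and partial relief, which are defined explicitly with 2 points. The 3-point gloss is attached only to the 3-month primary endpoint.
- *Three points should be the default, with identical medication conditions for both components.* Nothing ranks the parenthesis above the fuller definition, and different conditions for the two components are a permissible choice.

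The power figures are also open to challenge. The model has no source in the article, and it ignores the medication conditions, the route through a score of 0 and the bounded scale. That stands, and they are offered as illustration only.

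**Conclusion.** The primary endpoint is wrong as written and must be reconciled. This conclusion rests on the text alone: the section sets 3 points and 2 points for the same endpoint, and its primary-endpoint sentence lacks the medication conditions that the component definitions impose. The statements in the Abstract and in Statistical analysis do not decide between them.

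The effect on individual classification is certain. The effect on response rates and power cannot be computed from the article, which gives neither the share of patients with a 2-point fall nor the threshold behind 93.3% and 59.9%. Under the assumed rounded-normal scores with SD 1.5 to 3, power moves from about 81.5% to between 57% and 71%, or to between 88% and 91%, depending on which definition the planning rates follow. A reader might infer that the trial is underpowered; the document does not establish that.

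**What to change.** Before any outcome data are reviewed:

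1. Reconcile the sentences to one response threshold, stated expressly as a reduction from baseline at the index site, and use it wherever the primary endpoint is defined.
2. State in the primary-endpoint sentence whether the medication conditions of the complete and partial definitions apply to it.
3. Choose the threshold to match the definition that produced 93.3% and 59.9% in the feasibility cohort, where this can be established, and record the reason for the choice.
4. Report the other threshold as a pre-specified sensitivity analysis.

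The cost is a wording amendment. Trial status says that accrual opened in May 2020 and that amendments go through sponsor review and the IRB, so the process is not free. No new data are needed, because pain scores and pain medication are already recorded under Table 1.
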